# FORESEEABLE RISKS AND DISCOMFORTS

Provide a brief description of any foreseeable risks and discomforts to subjects. Include those related to drugs/devices/procedures being studied and/or administered/performed solely for research purposes. In addition, include psychosocial risks, and risks related to privacy and confidentiality. When applicable, describe risks to a developing fetus or nursing infant.

The risks entailed in this study are minor and include the minor discomfort and risk of bruising from obtaining blood samples. The total volume of blood obtained over the course of the five-month study will be about 2 times the amount usually given in a single blood donation.

The glucagon stimulated c-peptide test is commonly used in experimental protocols. The glucagon injection may be associated with mild nausea which usually dissipates in 5 minutes. Rarely (less than 1 in 20) subjects may vomit after glucagon.

The tuberculosis test is associated with minimal brief discomfort and, if positive, results in a small lump at the site of the injection.

The saline “vaccination” is associated with minimal, brief discomfort.

BCG vaccinations have been used for more than 30 years in many countries, including Canada and in western Europe, as a vaccination against tuberculosis. The recognized side effects of BCG vaccination include mild local discomfort at the vaccination site with a papular rash developing at the site 10-14 days after vaccination and reaching a maximal diameter of 3 mm 4-6 weeks after vaccination. The rash may scale thereafter, and may leave a visible scar. Local adenopathy is rarely seen in children, but almost never in adults. Rare events include osteomyelitis, lupoid reactions, disseminated BCG infections and death. The frequency of these severe reactions is between 1 in 1,000,000 and 1 in 5,000,000 vaccinations, and have occurred almost exclusively in immunosuppressed children.

Most of the recent experience with BCG has been in the intravesicular treatment of bladder cancer, where weekly instillations of BCG are performed for > 6 weeks.

After BCG vaccination, the tuberculosis skin test (PPD) is no longer reliable and regular chest x-rays may be necessary for specific jobs (teachers, health care workers). Finally, BCG vaccination has been used in Type 1 diabetes without any adverse consequences noted.

**EXPECTED BENEFITS**

# Describe both the expected benefits to individual subjects participating in the research and the importance of the knowledge that may reasonably be expected to result from the study. Provide a brief, realistic summary of potential benefits to subjects, for example, “It is hoped that the treatment will result in a partial reduction in tumor size in at least 25% of the enrolled subjects.” Indicate how the results of the study will benefit future patients with the disease/condition being studied and/or society, e.g., through increased knowledge of human physiology or behavior, improved safety, or technological advances.

BCG vaccination may be protective against tuberculosis, although it is not routinely used in the US. In addition to the general benefit of providing insight into the pathogenesis of Type 1 diabetes and the possible development of a treatment that may result in cure, the patients who participate in this preliminary trial may be eligible for further studies that will determine whether this approach can restore beta cell mass and function, relieving them of their need to administer insulin. The data collected in this phase of the investigation will be applicable in future phases.

**EQUITABLE SELECTION OF SUBJECTS**

The risks and benefits of the research must be fairly distributed among the populations that stand to benefit from it. No group of persons, for example, men, women, pregnant women, children, and minorities, should be categorically excluded from the research without a good scientific or ethical reason to do so. Please provide the basis for concluding that the study population is representative of the population that stands to potentially benefit from this research.

The population selected will represent the majority of persons with Type 1 diabetes who might benefit from reversal of the disease.

When people who do not speak English are excluded from participation in the research, provide the scientific rationale for doing so. Individuals who do not speak English should not be denied participation in research simply because it is inconvenient to translate the consent form in different languages and to have an interpreter present.

Type 1 diabetes, a rare disease, is even more rare in Hispanic populations. That said, the MGH Diabetes Center has investigators and staff who are fluent in Spanish. Potential participants who are Spanish-speaking will not be excluded.

For guidance, refer to the following Partners policy:

Obtaining and Documenting Informed Consent of Subjects who do not Speak English

[**http://healthcare.partners.org/phsirb/nonengco.htm**](http://healthcare.partners.org/phsirb/nonengco.htm)

**RECRUITMENT PROCEDURES**

Explain in detail the specific methodology that will be used to recruit subjects. Specifically address how, when, where and by whom subjects will be identified and approached about participation. Include any specific recruitment methods used to enhance recruitment of women and minorities.

Clinical physicians at the MGH Diabetes Center will discuss the study with Type 1 diabetic patients during their regular visits. If the patients express interest to their physicians, a study coordinator will meet with them and describe the study. Patients who are interested will be provided with the informed consent to take home. Those who are interested will return to the Diabetes Center for a scheduled screening visit during which informed consent will be obtained by the study physician.

We may also utilize advertisements to recruit diabetic and non-diabetic subjects. All advertisements will be submitted to the IRB for approval before use.

Type 1 diabetes mellitus affects men and women equally and we expect approximately 50% women. However, Type 1 diabetes mellitus is relatively rare in minority (African-American and Hispanic) populations, and extremely rare in persons of Asian descent. We will make every effort to identify minority patients with Type 1diabetes and recruit them to the study.

Provide details of remuneration, when applicable. Even when subjects may derive medical benefit from participation, it is often the case that extra hospital visits, meals at the hospital, parking fees or other inconveniences will result in additional out-of-pocket expenses related to study participation. Investigators may wish to consider providing reimbursement for such expenses when funding is available

All expenses related to the study will be covered by the grant, including travel and parking. If research subjects attend visits during mealtimes, incurring possible out of pocket expenses, the study will reimburse them for their meals.

For guidance, refer to the following Partners policies:

Recruitment of Research Subjects

[**http://healthcare.partners.org/phsirb/recruit.htm**](http://healthcare.partners.org/phsirb/recruit.htm)

Guidelines for Advertisements for Recruiting Subjects

[**http://healthcare.partners.org/phsirb/advert.htm**](http://healthcare.partners.org/phsirb/advert.htm)

Remuneration for Research Subjects

[**http://healthcare.partners.org/phsirb/remun.htm**](http://healthcare.partners.org/phsirb/remun.htm)

#### CONSENT PROCEDURES

Explain in detail how, when, where, and by whom consent is obtained, and the timing of consent (i.e., how long subjects will be given to consider participation). For most studies involving more than minimal risk and all studies involving investigational drugs/devices, a licensed physician investigator must obtain informed consent. When subjects are to be enrolled from among the investigators’ own patients, describe how the potential for coercion will be avoided.

The study will be discussed with Type 1 diabetic patients in the MGH Diabetes Center by their clinic physicians during their regular visits. If the patients express interest to their physicians, a study coordinator will meet with them and describe the study. Patients who are interested will be provided with the informed consent to take home. Subjects responding to advertisements will also be provided with a copy of the consent. Those who are interested will return to the Diabetes Center for a scheduled screening visit during which informed consent will be obtained by the study physician.

Potential volunteers will have as long to consider joining the study as necessary. They will be encouraged to bring family members with them to discuss any concerns. An independent Diabetes Investigator-Physician who is not directly involved with the current study will obtain informed consent from any patients of the Principal Investigator who express interest in joining the study in order to ensure that overt or subtle coercion has not played a role in their volunteering for the study.

NOTE: When subjects are unable to give consent due to age (minors) or impaired decision-making capacity, complete the forms for Research Involving Children as Subjects of Research and/or Research Involving Individuals with Impaired Decision-making Capacity, available on the New Submissions page on the PHRC website:

**[http://healthcare.partners.org/phsirb/newapp.htm#Newapp](http://healthcare.partners.org/phsirb/newapp.htm" \l "Newapp)**

For guidance, refer to the following Partners policy:

Informed Consent of Research Subjects

[**http://healthcare.partners.org/phsirb/infcons.htm**](http://healthcare.partners.org/phsirb/infcons.htm)

## DATA AND SAFETY MONITORING

Describe the plan for monitoring the data to ensure the safety of subjects. The plan should include a brief description of (1) the safety and/or efficacy data that will be reviewed; (2) the planned frequency of review; and (3) who will be responsible for this review and for determining whether the research should be altered or stopped. Include a brief description of any stopping rules for the study, when appropriate. Depending upon the risk, size and complexity of the study, the investigator, an expert group, an independent Data and Safety Monitoring Board (DSMB) or others might be assigned primary responsibility for this monitoring activity.

NOTE: Regardless of data and safety monitoring plans by the sponsor or others, the principal investigator is ultimately responsible for protecting the rights, safety, and welfare of subjects under his/her care.

An independent Data Safety Monitoring Board, with expertise in clinical immunology and diabetes, will be formed and will be charged with overseeing the study for safety and efficacy. Any severe adverse events, as well as a summary of all vaccine related events, will be reported to the DSMB in parallel with reporting such events to the HRC and FDA. Absent such events, the progress of the study with regard to adverse events and outcomes (results of T-cell measures and cytokine measurements, in particular) will be reviewed with the DSMB after the first 6 subject pairs (3 diabetics treated with the active vaccine) have completed the study.

Describe the plan to be followed by the Principal Investigator/study staff for review of adverse events experienced by subjects under his/her care, and when applicable, for review of sponsor safety reports and DSMB reports. Describe the plan for reporting adverse events to the sponsor and the Partners’ IRB and, when applicable, for submitting sponsor safety reports and DSMB reports to the Partners’ IRBs. When the investigator is also the sponsor of the IND/IDE, include the plan for reporting of adverse events to the FDA and, when applicable, to investigators at other sites.

NOTE: In addition to the adverse event reporting requirements of the sponsor, the principal investigator must follow the Partners Human Research Committee guidelines for Adverse Event Reporting

See above

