- HIV antibody negative
- Normal CBC
- Negative intermediate PPD test performed and read by study staff
- HCG negative (females)

The complete Diabetic subject exclusion criteria are:

- History of chronic infectious disease, such as HIV
- History of tuberculosis, TB risk factors, or history of + PPD, or BCG vaccination
- Treatment with glucocorticoids (other than intermittent nasal steroids) or disease or condition likely to require steroid therapy
- History of HIV
- Other conditions or treatments associated with increased risk of infections such as patients with a previous history of severe burns, or treatment with immunosuppressive medications of any type (e.g. imuran, methotrexate, cyclosporine, etanercept, infliximab) for any reason
- Current treatment with aspirin > 160 mg/day or chronic, daily NSAIDs
- Fasting or stimulated (1 mg glucagon stimulation test) c-peptide > 0.2 pmol/mL
- History of keloid formation
- HbA1c > 8.0%
- Pregnant or not using acceptable birth control
- Living with someone who is immunosuppressed and/or at high risk for infectious diseases (for example HIV+ or taking immunosuppressive medications for any reason)

Control Non-diabetic Subjects inclusion criteria:

- Age 18-55, no history of autoimmune diseases or diabetes
- No history of HIV
- No history of autoimmune disease or type 1 diabetes (use of insulin continuously since diagnosis) in first degree family members

Briefly describe study procedures. Include any local site restrictions, for example, “Subjects enrolled at Partners will not participate in the pharmacokinetic portion of the study.” Describe study endpoints.

The study will be performed in the outpatient MGH Diabetes Center or in the outpatient General Clinical Research Center. After initial screening, including obtaining baseline blood tests and performing a standard PPD test, diabetic subjects will be randomly assigned to receive either a saline (placebo) or the BCG vaccination. Weekly blood tests will track changes in t-lymphocytes and TNF levels. The BCG vaccination will be repeated 4 weeks after the initial vaccination and will be followed by monitoring for another 16 weeks. Including the screening tests, seventeen visits to the outpatient Diabetes Center or GCRC will be required over the 20-week study. Except for visits three and eight, which will require approximately 3 hours, the visits will take less than 15 minutes.

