## MONITORING AND QUALITY ASSURANCE

Describe the plan to be followed by the principal investigator/study staff to monitor and assure the validity and integrity of the data and adherence to the IRB-approved protocol. Specify who will be responsible for monitoring, and the planned frequency of monitoring. For example, specify who will review the accuracy and completeness of case report form entries, source documents, and informed consent.

NOTE: Regardless of monitoring plans by the sponsor or others, the principal investigator is ultimately responsible for ensuring that the study is conducted at his/her investigative site in accordance with the IRB-approved protocol, and applicable regulations and requirements of the IRB.

The PI and study coordinator will be responsible for overseeing the quality assurance regarding the conduct of the study.

Adherence to the protocol, including strict adherence to the eligibility criteria for recruitment, oversight of vaccinations and safety monitoring, and collection of data will be examined on a regular basis, need for corrective actions noted, and follow-up to determine that any identified problems are rectified will be the responsibility of the PI. Any outside (non-MGH) laboratory, including commercial laboratories, will be reviewed to ensure that quality control is at a level that is consistent with clinical research.

The PI will present a summary of the monitoring to the DSMB on a regular basis, and no less frequently than every 6 months.

For guidance, refer to the following Partners policies:

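### Prompt reporting to the DSMB depends on an undefined word, severe, or on vaccine-relatedness, and never on seriousness, which leaves a narrow gap for serious events judged unrelated

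*Protocol*

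**What the plan says.** The DSMB reporting rule is in the protocol section Data and Safety Monitoring. The prompt route is: "Any severe adverse events, as well as a summary of all vaccine related events, will be reported to the DSMB", and this happens "in parallel with reporting such events to the HRC and FDA".

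The default route follows. "Absent such events, the progress of the study with regard to adverse events and outcomes" is reviewed with the DSMB "after the first 6 subject pairs (3 diabetics treated with the active vaccine) have completed the study". The section schedules no later adverse-event review.

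The same section then asks for the investigator's own plan for reviewing and reporting adverse events. The answer only points back to the text above it, so the two sentences quoted here are the whole reporting plan. The form's printed note adds that "the principal investigator must follow the Partners Human Research Committee guidelines for Adverse Event Reporting"; it does not mention the DSMB.

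One further contact with the DSMB is stated, under Monitoring and Quality Assurance: "The PI will present a summary of the monitoring to the DSMB on a regular basis, and no less frequently than every 6 months".

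**The concern.** *Severe* describes how intense an event is. *Serious* describes its outcome, such as a hospitalisation or death. The two overlap but are not the same, and the prompt-reporting rule uses only the first, together with vaccine-relatedness.

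A hospitalisation that staff do not call severe and judge unrelated to the injection meets neither condition. Whether an event is unrelated is a judgement that an independent board should be able to check, yet under this wording that judgement helps decide whether the board hears of the event promptly.

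The point has some weight here because the only objective criterion stated for withholding the second injection, under Minimization of Risk and again under Ensuring Subject Safety, concerns inflammation or scarring related to the vaccination. Systemic events have no comparable stated criterion, so independent review of them matters more.

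**Working it through.** The protocol gives no figure for this point that could be reproduced. The check compares the relevant texts and adds simple timing arithmetic.

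**1. What each text covers**

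| Place in the protocol | What it provides | Does it catch a serious event that is not called severe and is judged unrelated? |
|---|---|---|
| Data and Safety Monitoring, first limb of the trigger | Severe events, undefined | No, if *severe* is read as intensity |
| Data and Safety Monitoring, second limb | Summary of vaccine-related events | No |
| Data and Safety Monitoring, default | Review after six completed pairs | Yes, but late |
| Data and Safety Monitoring, printed note | Duty under the Human Research Committee guidelines | Not stated for the DSMB |
| Monitoring and Quality Assurance | Summary at least every 6 months | Possibly; adverse-event listings are not promised |

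**2. Is *severe* defined elsewhere?** No. Under Foreseeable Risks and Discomforts the word covers osteomyelitis, lupoid reactions, disseminated infection and death. The only scale mentioned is an unspecified one for inflammation and scarring. Neither amounts to a definition for general adverse events.

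**3. How long could such an event wait?**

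Inputs:
- Second injection 4 weeks after the first, then 16 weeks of monitoring (Research Design and Methods): 4 + 16 = 20 weeks. This agrees with the stated duration: "seventeen visits to the outpatient Diabetes Center or GCRC will be required over the 20-week study".
- Six-pair review: after all six pairs have completed.
- Time from the start of the first pair to the start of the sixth: not stated. Call it *s* weeks.
- Event in the first pair at week *t*.

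The earliest six-pair review is at week *s* + 20, so the wait is *s* + 20 − *t*.

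- All six pairs start together (*s* = 0), event at *t* = 5: 0 + 20 − 5 = 15 weeks.
- *s* = 6 (assumption), *t* = 5: 6 + 20 − 5 = 21 weeks.
- *s* = 12 (assumption), *t* = 5: 12 + 20 − 5 = 27 weeks.

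The choice of week 5 is illustrative. An event soon after the first injection would wait about 20 weeks plus *s*.

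**4. Does the six-monthly summary shorten this?** Six months is about 26 weeks. Suppose that the summary lists adverse events and that its clock starts with the first pair; the protocol states neither. A summary at the maximum interval then precedes the six-pair review only if *s* + 20 > 26, that is *s* > 6. For the week-5 event the wait would be 26 − 5 = 21 weeks. More frequent summaries would shorten it, but none is fixed.

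**5. Could others be vaccinated meanwhile?** If all six pairs start together, all their scheduled second injections fall at week 4. The week-5 event then precedes none of them. For an event at week 4 or later, continued vaccination during the wait requires staggered entry or enrolment beyond the sixth pair. Both are plausible, since the section states no pause in enrolment, but the accrual rate is not given and the exposure cannot be quantified.

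**The case against.** The strongest reply is that *severe* was meant as *serious*. Two things support it. The rule ties these events to reports to the Human Research Committee and FDA, which suggests an externally reportable class and not an intensity grade. The only other use of the word for events, introduced by "The frequency of these severe reactions is between 1 in 1,000,000 and 1 in 5,000,000 vaccinations", refers to a list that includes death and disseminated infection. The protocol also has no general intensity scale on which a hospitalisation could be graded as less than severe. This stands as a likely explanation, and it limits the point. It does not remove it, because the protocol never states that meaning and a reporting trigger should not be open to two readings.

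A second reply is that the monitoring summarised to the DSMB expressly includes oversight of safety monitoring, and that 6 months is a maximum interval. That is correct, and the summary may carry safety content. It still promises no adverse-event listing and is not prompt.

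A third is that institutional reporting guidelines may define the reportable class. They are not available here, so this cannot be settled. As cited, they bind the investigator and say nothing about the DSMB.

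Three stronger conclusions may occur to a reader, and the protocol does not support them:
- *That the prompt trigger would almost never fire, at most once per 1,000,000 vaccinations.* That rate is for particular reactions to BCG. The rule covers severe events of any cause, and those reactions would in any case be caught as vaccine-related.
- *That the DSMB is the only independent safety oversight.* The Human Research Committee and FDA also receive reports.
- *That a difference between BCG and saline would go unseen because of this wording.* With about three BCG-treated diabetic subjects in the first six pairs, single prompt reports would hardly reveal one.

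**Conclusion.** The point holds as a minor defect of wording in a stated safety rule. Prompt reporting to the DSMB turns on an undefined term or on vaccine-relatedness, and no seriousness criterion appears anywhere in the protocol.

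The gap is narrow: the event must be serious, not called severe, and judged unrelated. Such an event need not reach the DSMB before the six-pair review, at least 20 weeks after the sixth pair starts, unless the monitoring summary happens to include it. The conclusion rests on a literal reading of *severe*. If the sponsor meant *serious* whatever the attribution, only the wording needs correcting. The point does not affect the trial's statistical results.

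**What to change.** In Data and Safety Monitoring, replace the opening words of the trigger sentence with: *Any serious adverse events, whatever the attribution, and any severe adverse events*. Keep the summary of vaccine-related events, and keep the reporting in parallel with the Human Research Committee and FDA.

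The cost is one phrase in the protocol and a few additional expedited reports to the DSMB in a small pilot study.
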